3.5 General care

Close attention to thermoregulation and fluid balance is recommended. Minimal handling and suctioning is recommended. Fluid and electrolyte management is left to the discretion of the attending physician, but data will be collected on total fluid intake, serum sodium levels, and sodium bicarbonate infusions.

3.6 Co-interventions and contamination

Co-interventions will be minimized by randomization, since all groups should be affected approximately equally. However, note will be made of interventions that could potentially alter outcome variables, such as fluid management. The major contaminant is that neonates with elevated A-a DO2 are a heterogeneous population with variable degrees of V/Q mismatch and right to left shunting and may not respond either in the same direction or magnitude to any intervention, including the administration of NO. However, this study is a pilot study to evaluate the effect of NO administered by oxygen hood in a "real-world" situation where heterogeneity is the rule, and transition from fetal to neonatal physiology is occurring. Another possible contaminant is that the NO group will have a slightly lower FiO2 (about 95-96% rather than 97-98% in the oxygen hood, due to admixture of the nitrogen carrier gas) than the oxygen group, and this will place the NO group at a disadvantage regarding the delivered oxygen concentration. However, similar small decreases in FiO2 occur even with NO use during mechanical ventilation and this is considered acceptable practice, since the improvements in oxygenation with NO are considered to outweigh the decreases due to the small reduction in FiO2.

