This study is designed as a pilot study to evaluate the physiologic efficacy (rather than effect on clinical outcomes) of NO administered by hood in improving oxygenation of neonates with elevated alveolar - arterial oxygen gradients (A-a DO2). If this is shown to be achievable, subsequent larger trials can determine if this method of NO administration can decrease the need for mechanical ventilation, ECMO, or other major outcomes.

1.1 Primary outcome measure:

Partial pressure of oxygen in post-ductal arterial blood (PaO2)

1.2 Secondary outcome measures:

1. Alveolar-arterial oxygen gradient (A-a DO2) after one hour of exposure to treatment gas
2. Alveolar-arterial oxygen ratio (A/a O2)
3. Oxygen saturation by pulse oximetry (SpO2)
4. Need for mechanical ventilation
5. Duration of oxygen therapy
6. Methemoglobin level in post-ductal arterial blood (MetHb)*
7. Platelet count*
8. Systemic blood pressure*
9. Environmental NO and NO2 exposure*

(* Safety indicators)

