1.3 Hypotheses

The primary hypothesis is that administration of nitric oxide gas by oxygen hood at 20 ppm to neonates with elevated A-a DO2 (500-600 mmHg) significantly increases PaO2, as compared to placebo gas (oxygen), within one hour of initiation, and with no significant adverse effects.

Secondary hypotheses

1. Administration of nitric oxide decreases A-a DO2as compared to placebo gas (oxygen)
2. Administration of nitric oxide decreases A/a O2 as compared to placebo gas (oxygen)
3. Administration of nitric oxide increases SpO2 as compared to placebo gas (oxygen)
4. Administration of nitric oxide decreases the need for mechanical ventilation as compared to placebo gas (oxygen)
5. Administration of nitric oxide at 20 ppm by oxygen hood does not increase duration of oxygen therapy significantly as compared to placebo gas (oxygen)
6. Administration of nitric oxide at 20 ppm by oxygen hood does not increase MetHb significantly as compared to placebo gas (oxygen)
7. Administration of nitric oxide at 20 ppm by oxygen hood does not decrease platelet counts significantly as compared to placebo gas (oxygen)
8. Administration of nitric oxide at 20 ppm by oxygen hood does not decrease mean systemic blood pressure significantly as compared to placebo gas (oxygen)
9. Administration of nitric oxide at 20 ppm by oxygen hood does not increase environmental NO and NO2 significantly as compared to placebo gas (oxygen)

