After entry criteria are met, informed consent is obtained from the parents by either the study coordinator, research nurse, or attending physician/fellow and the neonate will be randomized to either the NO group or control group. The treatment gas will be administered by hood, with the clinicians and nurses blinded to assignment. The apparatus setup at the bedside would be identical for both groups and the NO flowmeter and NO/NO2 concentrations will be masked. FiO2 and NO/NO2 concentrations of the inflow gas will be monitored at the beginning of the study period and the sensors will then be moved to the inner hood. Respiratory therapists will adjust flow and blending to administer 20 ppm of NO or an equivalent flow of O2. FiO2 and NO/NO2 concentrations in the inner hood will be monitored continuously for the study period. Physicians and nurses caring for the patient and analyzing results will be blinded to patient assignment. After completion of one hour on the study, the gas will be weaned every hour over the next four hours (20 ppm at 1 hour to 10 ppm at 2 hours to 5 ppm at 3 hours to 2.5 ppm to 4 hours to 0 ppm at 5 hours), then discontinued. If marked deterioration (decrease in oxygen saturation of > 5%) is seen during the weaning phase, the treatment gas can be increased to the previous level and can then be weaned subsequently by the same decrement but over two hours. The attending physician can initiate mechanical ventilation at any point during this study, based on clinical or other grounds. If methemoglobinemia (MetHb>5%) occurs, or if NO2 concentrations are >3% in the inner hood, or if oxygenation decreases significantly (decrease in oxygen saturation of > 5%), or if other adverse reactions that could possibly be related temporally to the treatment gas are evident, the gas is to be weaned in a shorter timespan (50% every 15 minutes). The results of these neonates will still be analyzed based on "intention to treat". If at the end of the study period the infant still meets entry criteria, he/she will be crossed over into the other treatment group.

Monitoring:

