3.8 Outcomes and definitions

1. PaO2: Partial pressure of oxygen in post-ductal arterial blood
2. A-a DO2 : calculated by PAO2 - PaO2

where PAO2 = [FiO2 x (PB - 47)] - PaCO2

PB= ambient barometric pressure in mm Hg

1. A/a O2 : calculated by PAO2 / PaO2

where PAO2 = [FiO2 x (PB - 47)] - PaCO2

1. SpO2: Oxygen saturation by pulse oximetry (pre-ductal)

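### Section 3.6 treats the lower FiO2 on NO only as a handicap; for A-a DO2 the same gap tilts secondary hypothesis 1 towards NO

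*Protocol*

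**What the plan says.** Section 3.6 lists the FiO2 difference as a possible contaminant. It puts FiO2 on NO, compared with oxygen, at "about 95-96% rather than 97-98% in the oxygen hood" and attributes the gap to nitrogen in the NO supply. Its conclusion for the NO arm is that "this will place the NO group at a disadvantage regarding the delivered oxygen concentration". The section accepts this because the gain from NO is considered larger than the loss from the lower FiO2. It does not mention A-a DO2 as an outcome.

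In section 3.8, A-a DO2 is alveolar minus arterial oxygen pressure, and the alveolar term is given by "where PAO2 = [FiO2 x (PB - 47)] - PaCO2". Section 1.2 lists as the first secondary outcome "Alveolar-arterial oxygen gradient (A-a DO2) after one hour of exposure to treatment gas", so it is measured while the gas is running. Secondary hypothesis 1 in section 1.3 reads "Administration of nitric oxide decreases A-a DO2as compared to placebo gas (oxygen").

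Section 3.4 states that "FiO2 and NO/NO2 concentrations in the inner hood will be monitored continuously for the study period". It also gives about 97% oxygen in the inner hood with NO at about 20 ppm, which does not match the 95-96% in section 3.6.

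**The concern.** FiO2 enters A-a DO2 with a positive sign. A lower FiO2 in one arm therefore lowers A-a DO2 in that arm even if the lungs and the treatment do nothing. A reader of section 3.6 would take the FiO2 gap to be conservative throughout, since it is described only as working against NO. For the first secondary outcome it works the other way.

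The trial is meant to show physiologic efficacy. A significant fall in A-a DO2 would naturally be read as supporting the PaO2 result, or as a signal in its own right if PaO2 missed significance. Part or all of that fall could be nitrogen dilution.

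**Working it through.** **The plan's own figure.** Section 3.9 gives 85% power with 20 per group, alpha 0.05, a difference of 25% and an SD of 25% of the mean (standardised difference 1). A two-sided unpaired t-test gives 86.9%, so the figure is reproduced within 2 points. The same test is used below.

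**Inputs from the protocol.** FiO2 0.95-0.96 on NO and 0.97-0.98 on oxygen (3.6), a gap of 1 to 3 points with midpoint 2. Formula from 3.8. 20 per arm (3.9).

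**Assumptions.** Barometric pressure (PB) 760 mm Hg and PaCO2 40 mm Hg. The protocol gives no SD for A-a DO2. The 29 mm Hg used here is the SD of a uniform spread over the 500-600 entry window (100/√12 = 28.9); other values are shown.

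**Step 1: the formula alone.** The arm difference (NO minus oxygen) is

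ΔA-a DO2 = (PB − 47) × ΔFiO2 − ΔPaCO2 − ΔPaO2.

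With PaO2 and PaCO2 equal in the two arms:
- 1 point: 713 × 0.01 = 7.1 mm Hg lower on NO
- 2 points: 713 × 0.02 = 14.3 mm Hg lower
- 3 points: 713 × 0.03 = 21.4 mm Hg lower

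Example at PaO2 100: on oxygen 0.975 × 713 − 40 − 100 = 555.2; on NO 0.955 × 713 − 40 − 100 = 540.9. At PB 740 the range is 6.9 to 20.8.

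**Step 2: let PaO2 fall with FiO2.** ΔPaO2 carries a minus sign, so a passive fall in PaO2 cancels part of step 1. This was checked with a fixed-shunt oxygen-content model (assumed Hb 14-20 g/dL, P50 20-27 mm Hg, arteriovenous difference 4 mL/dL). With a 2-point gap and a starting PaO2 of 75-170 mm Hg, PaO2 falls by 0.7 to 10.6 mm Hg and A-a DO2 still falls by 13.5 to 3.6 mm Hg. The net direction stays towards NO in every case. V/Q mismatch was not modelled and could offset more.

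**Step 3: effect on the test.** Chance of a significant result against zero with no NO effect (two-sided 0.05, 20 per arm, nominal 5%), for a 2-point gap:

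| A-a DO2 artefact | SD 25 | SD 29 | SD 40 | SD 60 |
|---|---|---|---|---|
| 3.6 mm Hg (largest passive PaO2 fall) | 7% | 7% | 6% | 5% |
| 13.5 mm Hg (smallest passive PaO2 fall) | 38% | 30% | 18% | 11% |
| 14.3 mm Hg (no PaO2 fall) | 42% | 33% | 20% | 11% |

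**Step 4: the A/a ratio.** Section 3.8 defines it as PAO2/PaO2. PAO2 goes from 655.2 to 640.9, a fall of 2.2%, so the ratio falls only if PaO2 drops by less than 2.2%. In the shunt model (nine combinations of Hb and P50) it falls in seven at PaO2 75, in two at PaO2 100 and in none at 125 or above. The direction for A/a is therefore uncertain.

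**Step 5: the size of the gap.** Section 3.4's blend of 800 ppm NO in nitrogen taken to 24 ppm is 24/800 = 3% nitrogen; at 20 ppm it is 20/800 = 2.5%. If hood dilution is otherwise equal in the two arms, that implies a gap of 2.5 to 3 points, within the range of section 3.6. But setting section 3.4's 97% on NO against section 3.6's 97-98% on oxygen gives only 0 to 1 point (0 to 7 mm Hg). The documents do not settle this.

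**The case against.** **Section 3.6 is not wrong as written.** A reader might infer that it states the opposite of the truth about A-a DO2. It does not. Its sentence concerns delivered oxygen concentration, where NO is indeed at a disadvantage, and that is the right direction for the primary outcome. The fault is an omission. This stands.

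**The large false-positive rates need PaO2 to stay fixed.** Taking the formula alone, a reader could reach 33% at 2 points and 62% at 3 points (SD 29). Those figures assume that PaO2 does not respond to FiO2, which contradicts the very handicap that section 3.6 describes. They are ceilings. A wider spread at one hour is also plausible, since section 5.2 expects responses to differ in direction and magnitude, and it would lower the rates further.

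**The artefact arises only if measured FiO2 enters the formula.** With a nominal 1.0 it disappears. The protocol does not say which value is used, but continuous inner-hood monitoring makes the measured value the natural reading.

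**A shifted null is not the answer.** One might test A-a DO2 against the FiO2-expected difference instead of zero. Subtracting (PB − 47) × ΔFiO2 leaves exactly −(ΔPaO2 + ΔPaCO2). That nearly repeats the primary outcome, and it is biased against NO whenever PaO2 falls passively.

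**Entry is not affected.** One might extend the point to the 500-600 window. Section 3.2 has those gases taken on 100% oxygen before randomisation, and section 3.7 has the infant weaned to 100% oxygen before crossover is considered. The carrier-nitrogen gap applies at neither time.

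**Conclusion.** The point holds as an omission affecting one secondary outcome. By the protocol's own formula and FiO2 figures, carrier nitrogen lowers A-a DO2 on NO with no NO effect, and secondary hypothesis 1 tested against zero is tilted towards NO. At a 2-point gap the tilt is at most about 14 mm Hg (7 to 21 at 1 to 3 points, PB 760 assumed), and about 4 to 13.5 mm Hg under the assumed fixed shunt. At the assumed SD of 29 mm Hg this means about 7 to 30% false positives at 2 points, up to 33% if PaO2 does not fall at all, and less with a larger SD or a smaller gap.

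The documents do not support extending this to the A/a ratio, whose direction is uncertain, or to PaO2, where the gap works against NO. The size remains open until the oxygen figures in sections 3.4 and 3.6 agree.

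**What to change.** - **Section 3.6:** state the direction of the FiO2 gap separately: against NO for PaO2, towards NO for A-a DO2, uncertain for A/a.
- **Sections 3.4 and 3.6:** reconcile the inner-hood oxygen figures for the NO arm.
- **Section 3.8:** calculate A-a DO2 from the inner-hood FiO2 recorded at each blood gas. This makes the value correct but does not remove the tilt, so the next two items are needed as well.
- **Section 3.9, reporting:** report FiO2 by arm. Beside the unadjusted A-a DO2 comparison, show the FiO2-expected difference, (PB − 47) × (mean FiO2 on NO minus mean FiO2 on oxygen), as a bound on the artefact and not as a replacement null.
- **Section 3.9, interpretation:** do not count a fall in A-a DO2 as evidence of NO efficacy unless PaO2 also rises.

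The cost is wording and one extra reported line, since FiO2 is already monitored continuously. The downside is that the A-a DO2 result becomes less favourable to NO and adds little beyond PaO2.

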3.7 Study exit criteria

1. Completion of one hour on treatment gas followed by weaning to 100% oxygen by hood. If at the end of the study period the infant still meets entry criteria (A-a DO2 500- 600 mm Hg), he/she will be crossed over into the other treatment group.
2. If methemoglobinemia (MetHb>5%) occurs, or if NO2 concentrations are >3% in the inner hood, or if oxygenation decreases significantly (decrease in oxygen saturation of > 5%), or if other significant adverse reactions that could possibly be related temporally to the treatment gas are evident, the gas is to be weaned in a shorter timespan (50% every 15 minutes).
3. Sudden marked deterioration in any physiological variable, that in the opinion of the attending physician, requires initiation of mechanical ventilation or ECMO (initiation of inotropic support, change of intravenous fluid intake, or antibiotic therapy are not included in exit criteria).
4. Transfer to another institution / death / withdrawal from study by parent or attending physician

The study coordinator is to be contacted in cases where criteria 2, 3, or 4 are being considered.

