1. Apparatus: FiO2 and NO/NO2 concentrations will be checked in the **inflow gas** at the beginning, and continuous monitoring of FiO2 and NO/NO2 concentrations in the **inner hood** will be done till exit from study. FiO2 and NO/NO2 concentrations will also be measured **outside the hood** 30 min and one hour after commencement of the treatment, at a distance of one foot (30 cm) from the front of the hood.
2. Baby: **ABGs** at 0 hours (the last ABG before beginning treatment gas) and 1 hour will be used for the study. **MetHb** will also be measured in these samples. Frequency of ABG and other lab investigations at other times will be at the discretion of the attending physician, but should be at least q 1 hour for the five hours on the study. **Oxygen saturation, heart rate, respiratory rate** and **blood pressures** (by arterial catheter) will be monitored continuously through the period of study. A **platelet count** obtained less than 12 hours before entry into the study will also be compared with one obtained immediately after completion of one hour of exposure to the treatment gas. **Echocardiograms** are encouraged before entry into the study, as echocardiograms are usually part of the clinical investigation in neonates with suspected PPHN, but are not a pre-requisite for entry in view of time and technical constraints.

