3.9 Statistical issues

The power of the study is 85% with n=20 in each group, =0.05, assuming we need to detect a difference of 25 % with a standard deviation at 25% of the mean. Repeated measures ANOVA or unpaired t-test will be used if data are normally distributed, otherwise non-parametric tests will be used. Data will be analyzed by intention to treat. Small numbers are required since this is a pilot study to show physiologic efficacy of the technique and is not meant to study clinical outcomes.

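### Section 3.6 relies on randomization to equalize co-interventions, but inotropes or volume started after the gas begins are not balanced by it and can dilute the blood-pressure safety comparison

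*Protocol*

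**What the plan says.** - **Outcome.** Protocol 1.2 lists "Systemic blood pressure" as secondary outcome 8 and stars it as a safety indicator. Hypothesis 8 in 1.3 is that NO by hood "does not decrease mean systemic blood pressure significantly as compared to placebo gas (oxygen"). The primary hypothesis also includes the absence of significant adverse effects.
- **Measurement.** Under Monitoring in 3.4, pressures are taken "by arterial catheter) will be monitored continuously through the period of study". No time point for the comparison is given.
- **Staying in the study.** Exit criterion 3 in 3.7 concerns deterioration that requires ventilation or ECMO, and it adds that "initiation of inotropic support, change of intravenous fluid intake, or antibiotic therapy are not included in exit criteria".
- **Analysis set.** Section 3.9: "Data will be analyzed by intention to treat".
- **Co-interventions.** Section 3.6: "Co-interventions will be minimized by randomization, since all groups should be affected approximately equally". It then says that "note will be made of interventions that could potentially alter outcome variables, such as fluid management". Section 3.5 says that "data will be collected on total fluid intake, serum sodium levels, and sodium bicarbonate infusions". Neither section names inotropes, and the use of support is not among the nine secondary outcomes in 1.2.

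**The concern.** Randomization balances what exists before allocation. An inotrope or a volume bolus started during treatment gas comes afterwards. If the gas lowers systemic pressure, more infants on NO will be supported, and their later pressures will be raised by that support. The premise of 3.6, that all groups are affected about equally, then fails in exactly the case that hypothesis 8 is meant to examine.

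Two things follow. The difference in mean pressure shrinks towards zero, which favours the conclusion of no decrease. And part of the effect moves into unequal use of support, which no listed outcome compares. The error runs towards declaring safety, in newborns, on an indicator that the protocol itself marks as a safety measure.

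**Working it through.** **1. The plan's own figure.** Section 3.9 gives 85% power for 20 per group, alpha 0.05, a 25% difference and an SD of 25% of the mean. The standardized effect is 0.25/0.25 = 1.0. A two-sided unpaired t-test (noncentral t, 38 df, noncentrality 1.0 × √(20/2) = 3.16) gives 86.9%, so the figure reproduces. It concerns PaO2; the protocol states no power for blood pressure.

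**2. Inputs for blood pressure.** From the protocol: 20 per group, alpha 0.05, unpaired t-test (one of the tests that 3.9 names). Assumed for illustration, because the protocol gives none: control mean 48 mm Hg, SD 7, true fall on NO of 7 or 5 mm Hg, and support for any infant, in either arm, whose pressure is below a cut of 38, 40 or 42. The cuts only drive the calculation and are not proposed as clinical thresholds. Two assumptions about restoration bracket the result:
- *Full:* supported pressures become N(48, 4), the untreated mean.
- *To the cut:* supported pressures become N(cut, 2).

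**3. Share supported.** This is Φ((cut − mean)/SD). For a fall of 7 the NO mean is 41:
- cut 38: NO Φ(−0.43) = 33%, control Φ(−1.43) = 8%
- cut 42: NO Φ(0.14) = 56%, control Φ(−0.86) = 20%

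**4. Observed difference, worked for a fall of 7 and cut 38.** Arm mean after support = p × (restored mean) + μ(1 − p) + SD × φ(a), with a = (cut − μ)/SD and p = Φ(a).
- Full: NO 0.334 × 48 + 41 × 0.666 + 7 × 0.364 = 45.9; control 0.077 × 48 + 48 × 0.923 + 7 × 0.144 = 49.0; difference 3.1.
- To the cut: NO 0.334 × 38 + 41 × 0.666 + 7 × 0.364 = 42.5; control 0.077 × 38 + 48 × 0.923 + 7 × 0.144 = 48.2; difference 5.7.

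**5. Chance of a significant result** (20,000 simulated trials per setting; ranges over the three cuts):

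| True fall | No support | Full restoration | Restored to the cut |
|---|---|---|---|
| 7 mm Hg: observed difference | 7.0 | 2.3–3.1 | 4.4–5.7 |
| 7 mm Hg: detection | 87% | 31–43% | 78–84% |
| 5 mm Hg: observed difference | 5.0 | 1.9–2.7 | 3.4–4.3 |
| 5 mm Hg: detection | 59% | 23–32% | 51–57% |

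**6. Cross-check by a simpler model.** If a share f of NO infants has the fall fully corrected, a fall of d SD appears as d(1 − f). For d = 1.0, detection is 87% at f = 0, 69% at f = 0.2 and 34% at f = 0.5. The direction agrees and the size again depends on the assumptions.

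**7. Hypothesis 8 without any support.** For d = 0.5 and f = 0, detection is 34%, so such a fall is missed in about 66% of trials. Reading non-significance as safety, with no margin, is therefore a separate and larger weakness, to which the dilution adds.

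**The case against.** The strongest case on the other side has five parts.

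- **A reader might infer that the protocol has the test use supported pressures.** It does not say so. That follows from intention to treat plus silence, and a statistical analysis plan, not shown, may fix the time point and the handling of pressures after support. This stands, so the point is about the default. It does not rescue the sentence in 3.6, which is in the protocol and is wrong whatever a later plan says.
- **A reader might infer that hypotension would be hidden.** The documents do not support that. Pressure is recorded continuously, so values before support exist. Total fluid intake is collected. Exit criterion 2 in 3.7 provides for faster weaning and contact with the coordinator when a significant adverse reaction may be linked in time to the gas. Dilution is the accurate word.
- **Recording may already be adequate.** The note promised in 3.6 is open-ended, with fluids only as an example, and the data collection form (Appendix B) is not in the text at hand. This stands: it cannot be said that inotropes go unrecorded. What is missing is any comparison of support by arm among the outcomes in 1.2.
- **The size is assumption-driven.** This stands. Moving only the restoration level takes detection of a 7 mm Hg fall from 31–43% to 78–84%. The background in 2.2 also reports trials of NO without systemic hypotension, so a fall of a full SD may be pessimistic.
- **Masking protects the comparison.** Clinicians and nurses are blinded (3.4), which limits support given because the arm is known. It does not limit support given because pressure has fallen.

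**Conclusion.** The point holds as a flaw in the stated reasoning of 3.6, with a bias of known direction and unknown size. Support started in response to the gas is not balanced by randomization. Because supported infants stay in and analysis is by intention to treat, the default comparison for hypothesis 8 leans towards no decrease. Under the assumed mean, SD and cuts, detection of a 7 mm Hg fall drops from about 87% to somewhere between 31% and 84%. With little support given, the loss would be small.

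Two further readings should be resisted. Keeping supported infants in the study is not an error: it agrees with intention to treat, and nothing here argues for removing them. Nor should the main analysis switch to the last pressure before support. That takes a low value at a variable time, chosen by an event after randomization, and answers a different question. The change is worth making because it is cheap and the bias favours a safety claim.

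**What to change.** - **3.6:** replace the sentence on randomization with one saying that co-interventions begun after randomization may depend on the treatment gas, are not balanced by randomization, and will be reported by arm.
- **3.5 or the data form:** record each start or increase of an inotrope, and volume given for pressure, during treatment gas, with its time.
- **1.2 item 8 and hypothesis 8:** beside mean pressure, compare by arm the proportion of infants with such support, with a confidence interval, as a safety outcome.
- **Mean pressure:** keep all infants in the intention-to-treat comparison, and show pressure before support as a descriptive supplement only.

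**Cost:** one data item, if the form does not already hold it, one more safety table, and a few sentences. With 20 infants per group the interval for the proportions will be wide, so the table describes more than it tests. No change to clinical care or to the exit criteria is proposed.
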